## Abstract

**Background:**

Since the introduction of endovascular aortic repair (EVAR) for treatment of abdominal aortic aneurysms (AAAs), progressive improvements in results have been achieved. However, conventional bifurcated stent grafts have been proven to have a nonnegligible risk of failure and secondary intervention, principally due to the lack of adequate proximal sealing. The unique AFX 2 Endovascular AAA System (Endologix, Irvine, CA) unibody device, which provides different sealing and fixation features compared with conventional devices, seems to overcome these limitations.

**Objective:**

The aim of this study is to evaluate intraoperative, perioperative, and postoperative results in patients treated with the AFX 2 Endovascular AAA System endografts for elective AAA repair in a large cohort of consecutive patients.

**Methods:**

All eligible EVAR patients will be included in this observational, multicenter, prospective, nonrandomized study. The number of patients to be enrolled is 500.

**Results:**

The primary endpoint of the study is to evaluate the technical and clinical success of EVAR with unibody endografts in short- (90-day), mid- (1-year), and long-term (5-year) follow-up periods. The following secondary endpoints will also be addressed: operative time, intraoperative radiation exposure, contrast medium usage, AAA sac shrinkage at 12-month and 5-year follow-up, and any potential role of patients’ baseline characteristics and device configuration on primary endpoint. The actual start date of the investigation was November 2019. The final patient is expected to be treated by the end of December 2020, and the estimated study completion date is December 2025.

**Conclusions:**

This study will provide verified real-world data on AAAs treated by AFX 2 endografts and followed for a long-term interval.

**International Registered Report Identifier (IRRID):**

PRR1-10.2196/16959

## Introduction

In recent years, endovascular aortic repair (EVAR) has emerged as a safe and valid option for treatment of abdominal aortic aneurysms (AAAs) (Multimedia Appendix 1). The AFX 2 Endovascular AAA System (Endologix, Irvine, CA) consists of two components: an implantable stent graft and a disposable delivery catheter. The preloaded stent graft is transferred through the AFX 2 Introducer System and inserted endoluminally via the femoral or iliac artery over a guidewire and, upon deployment and withdrawal of the delivery system, expands to the indicated diameter. During deployment and expansion, the stent graft is intended to form proximal and distal seal zones surrounding the aneurysm location. The stent graft is composed of a cobalt-chromium alloy self-expanding stent cage with a thin-walled, low porosity expanded polytetrafluoroethylene graft cover that is attached proximally and distally to the stent cage with a polypropylene suture. The system consists of a unibody bifurcated stent graft, with proximal extension and limb extension accessory components available, as needed, to accommodate the patient’s specific anatomy.

The AFX 2 Endovascular AAA System is essentially composed of two distinct elements: the bifurcated stent graft and the proximal and iliac limb extension stent grafts.

The bifurcated element is the primary component that is delivered into the patient’s aorta. All bifurcated stent grafts consist of a unibody configuration (an aortic main body with two attached iliac legs). The main body and each iliac leg are constructed from a single wire. The main body is manufactured in sizes ranging from 22 mm to 28 mm. The iliac legs are 13 mm to 20 mm in diameter for all sizes of bifurcated stent grafts.

The proximal and iliac limb extension stent graft components are used to extend the lengths of implanted bifurcated components. The AFX 2 Endovascular AAA System proximal extensions (Vela) are available in suprarenal and infrarenal configurations and use a circumferential radiopaque marker for identification of the proximal graft fabric line.

According to current instructions for use, the following anatomical criteria are required.

Adequate iliac or femoral access compatible with the required delivery systems (diameter 6.5 mm)Nonaneurysmal aortic neck between the renal arteries and the aneurysm with a length 15 mm, a diameter ≥18 mm and ≤32 mm, and a neck angle ≤60° to the body of the aneurysmAortic length ≥1.0 cm longer than the body portion of the chosen bifurcated modelCommon iliac artery distal fixation site with a distal fixation length ≥15 mm, ability to preserve at least one hypogastric artery, a diameter ≥10 mm and ≤23 mm, and an iliac angle ≤90° to the aortic bifurcationExtension stent grafts must have the ability to overlap the bifurcated stent graft by at least 30 to 40 mm proximally and at least 15 to 20 mm distally

Some elegant papers have been published on this unique device [1-7]. In 2010, Carpenter et al [6] reported in a study of 157 patients treated by unibody device implantation in three different prospective multicenter trials (Powerlink trial, Powerlink XL trial, and Powerlink Suprarenal Extension trial). All enrolled patients were treated between 2000 and 2008 and followed through 5 years. Technical success was achieved in 99% of patients. Aneurysm exclusion was achieved in all patients over a mean procedure time of 132 (SD 58) minutes. No aneurysm related deaths, ruptures, conversions, or migrations have been observed to current follow-up, as these aneurysms have continued to remodel with more than 92% of patients free of sac growth. At each annual evaluation period, no stent fractures, material failures, or losses of patency were found by the core laboratory. During the follow-up period, 5 patients were treated for a Type Ia endoleak, 3 for a Type Ib, and 3 for a limb occlusion. All of these reinterventions were performed with a new endovascular procedure without needing surgical conversion [6].

Similar results were reported by Qu and Raithel [4] in their single center study on more than 600 patients. Among the 612 patients in the cohort, 99 cases (16%) completed between 1999 and 2004, had the endograft deployed from the renal artery downward. The remaining 513 (84%) had the bifurcated stent graft deployed onto the native bifurcation, and among those cases 146 (28%) were deemed as challenging anatomy with a short or angulated neck. Technical success was achieved in 98.5% of patients (603/612). Intraoperative conversion occurred in 9 patients: 8 delivery access failures and 1 rupture. Perioperatively, 3 deaths occurred, and 2 limb occlusions were encountered. The rates of late conversion in the renal fixation and anatomical fixation groups were 4.0% and 1.9%, respectively. Likewise, the cumulative rates of a type I proximal endoleak in the renal fixation and anatomical fixation groups were 5.0% and 1.2%, respectively. Remarkably, no stent fracture, graft disruption, or type III or type IV endoleak was observed in their experience. Freedom from aneurysm sac diameter increase was 96% [4].

Moreover, Silingardi et al [7] performed a comparative study to compare nephrotoxic contrast medium with radiation exposure during elective EVAR procedures using unibody and modular devices. The initial hypothesis was that the unique unibody device structure, associated with not needing a gate cannulation, could reduce total procedural and total fluoroscopy time, as well as reduce the volume of contrast medium needed. Their study on 60 unibody devices and 57 bifurcated devices confirmed the hypothesis. For unibody and bifurcated devices, the median surgical procedure duration was 75 min vs 105 min (*P*<.001), the median volume of iodine contrast injected was 85 ml vs 170 ml (*P*<.001), and the median fluoroscopy time was 350 sec vs 780 sec (*P*<.001), respectively [7].

The promising data from these studies should be confirmed by prospective data collecting in a large consecutive cohort of patients using the latest generation unibody device implantation. Therefore, this study aims to evaluate intraoperative, perioperative, and postoperative results in patients treated with AFX 2 Endovascular AAA System endografts for elective AAA repair in a large cohort of consecutive patients.

**Inclusion criteria**
Elective abdominal aortic aneurysm patients that should be treated by standard abdominal endovascular aneurysm repair, according to Endologix AFX unibody device’s instructions for usePatient is willing to comply with specified follow-up evaluations at the specified times for the duration of the studyPatient is >18 years of agePatient, or their legal representative, understands the nature of the procedure and provides written informed consent prior to enrollment in the study
**Exclusion criteria**
Abdominal endovascular aneurysm repair performed in urgent or emergent settingPatients treated outside Endologix AFX unibody device’s instructions for usePatients refusing treatmentPatients for whom antiplatelet therapy, anticoagulants, or antihypertensive drugs are contraindicatedPatients with a history of prior life-threatening contrast medium reactionLife expectancy is less than follow-up period

This study respects all the principles reported in the current version of the Helsinki declaration (2013). According to the current International Council for Harmonisation of Technical Requirements for Pharmaceuticals for Human Use and Good Clinical Practice guidelines, each investigator is responsible for the regularity of the study. The aim of these standards is to assure the safety and comfort of all people recruited in the study. The study protocol and the written informed consensus form will be submitted to the local ethics committees for review.

AAA morphology will be assessed by OsiriX MD (PIXMEO, Geneva, Switzerland) on a regular Mac OS computer in one preoperative, contrast-enhanced, computed tomography angiography (CTA) [8]. The CTA must be performed with a biphasic acquisition protocol (unenhanced and contrast-enhanced scanning with a bolus tracking system) and reconstructions of 1-mm slices. All measurements (diameter, length, and angle) will be evaluated on a workstation with dedicated reconstruction software for center lumen line analysis and multiplanar reconstruction.

A patient is considered enrolled in the study if there is full compliance with the study inclusion and exclusion criteria.

Clinical data will be collected at patient enrollment, the EVAR procedure, discharge, planned follow-ups (ie, 1-3 months and 12 months postprocedure, and yearly thereafter), unplanned or interim follow-ups, and patient death. CTAs are mandatory within 90 days and then at 1 and 5 years after the index procedure. The duplex ultrasound scan will be performed at the same follow-up interval and also at 24, 36, and 48 months. A new CTA will be performed in case of unexpected events during follow-up.

### Endpoints

The primary endpoint of the study is to evaluate the technical and clinical success of EVAR with unibody endografts in short- (90-day), mid- (1-year), and long-term (5-year) follow-up periods.

Technical success was defined as the correct graft deployment without any unintentional occlusion of the aortic visceral branches or both hypogastric arteries, with aneurysm exclusion confirmed by the intraoperative angiography, no signs of type I or III endoleak, or conversion to open surgery.

Clinical success included successful deployment of the endovascular device at the intended location without death as a result of aneurysm-related treatment, type I or III endoleak, graft infection or thrombosis, aneurysm expansion (>5 mm), aneurysm rupture, or conversion to open repair (OR), as well as the presence of graft dilatation of 20% or more by diameter, graft migration, or a failure of device integrity [9].

The clinical and technical success were defined as assisted in cases of unplanned endovascular procedures, or secondary if unplanned surgery is necessary.

The following secondary endpoints will be also addressed: operative time, intraoperative radiation exposure, contrast medium usage, AAA sac shrinkage at 12-month and 5-year follow-ups, and any potential role of patients’ baseline characteristics and device configuration on primary endpoint.

### Data Collection and Analysis

Patient data will be captured electronically using a computer-based platform accessible to all investigators. Descriptive data summaries will be used to present and summarize the collected data. For categorical variables such as gender, frequency distributions and cross tabulations will be given. For numeric variables such as patient age, minimum, maximum, mean, median, and standard deviation will be calculated. For all variables, a 95% confidence interval for the relevant parameters of the underlying distribution will be calculated. For all time-dependent events, life tables will be calculated using the Kaplan-Meier estimate method for a period starting on the date of the procedure up to and including all follow-up visits. Stratification to risk factors will be performed and the logrank test will be used to compare the different outcomes; associated *P*<.05 will be defined as significant.

All preoperative and follow-up CTAs were assessed and independently evaluated by two experienced vascular surgeons at core lab centers. Disagreements will be discussed and resolved by consensus.

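### The only comparison stated for the role of device configuration is a log-rank test across strata at P<.05, which can report anatomy as a configuration effect

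*Protocol article*

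**What the plan says.** The Endpoints section of the protocol article lists, among the secondary endpoints, the possible role of "baseline characteristics and device configuration on primary endpoint". The primary endpoint is the "technical and clinical success of EVAR with unibody endografts in short- (90-day), mid- (1-year), and long-term (5-year) follow-up periods".

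Data Collection and Analysis then gives the methods:

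- Time-to-event description: "For all time-dependent events, life tables will be calculated using the Kaplan-Meier estimate method".
- Comparison: "Stratification to risk factors will be performed and the logrank test will be used to compare the different outcomes", and "associated *P*<.05 will be defined as significant".
- Categorical variables: "For categorical variables such as gender, frequency distributions and cross tabulations will be given". A 95% confidence interval is promised for every variable.

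The log-rank test is the only test named in the article.

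Two other statements matter. The Introduction describes the device as a unibody graft with "proximal extension and limb extension accessory components available, as needed, to accommodate" the individual patient's anatomy. The section on objective and duration says that patients undergo the procedure according to preference, anatomy and operator experience. Technical success is judged in the operating room, "with aneurysm exclusion confirmed by the intraoperative angiography".

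**The concern.** The aim asks what part configuration plays in success or failure. Nobody is randomized to a configuration. By the article's own account, anatomy helps to decide which components are used, and anatomy may also affect failure. If patients are split by configuration and the curves are compared without adjustment, a difference can arise from anatomy alone. The test would then be right that the curves differ, but the conclusion that configuration plays a role would be wrong.

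The exclusion of patients treated outside the instructions for use narrows the anatomy but need not remove the link. The Introduction allows neck diameters of 18 to 32 mm, while main bodies run from 22 to 28 mm. It is an inference, not a statement in the article, that component choice still follows neck diameter within those limits.

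The set of baseline factors is also open-ended, and each P<.05 is to be called significant. The more factors are tested, the more likely it is that one with no effect is reported as a predictor.

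What is at stake is a secondary aim. The estimates of technical and clinical success themselves are not affected.

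**Working it through.** **What can be reproduced.** The plan's only figure here is the 0.05 threshold. One test at 0.05 has a 5% error rate. The 500 patients come from centre volumes, with no power, effect size or event count, so there is nothing further to reproduce.

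**1. Confounding of configuration by anatomy.** Inputs:

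- From the article: n = 500; 5-year follow-up; 28% with difficult anatomy (146/513 in the cited 612-patient single-centre series).
- Assumed: failure hazard of 0.02 per year in ordinary anatomy; the hazard ratio (HR) for difficult anatomy; the share receiving a given configuration in each anatomy group; no true configuration effect; no censoring before 5 years. There were 1000 runs per row.

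The expected number of failures is 500 × [0.72(1 − e^(−0.1)) + 0.28(1 − e^(−0.1·HR))]. This is about 54, 60 and 71 for HR 1.5, 2 and 3.

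| Configuration share, difficult vs other anatomy | Anatomy HR | Unadjusted log-rank rejects | Log-rank stratified by anatomy rejects |
|---|---|---|---|
| 50% vs 50% | 1.5 / 2 / 3 | 4.7% / 5.6% / 5.4% | 5.1% / 5.3% / 5.6% |
| 60% vs 40% | 1.5 / 2 / 3 | 6.7% / 7.7% / 14.0% | 5.2% / 5.0% / 5.2% |
| 70% vs 30% | 1.5 / 2 / 3 | 9.6% / 17.7% / 41.5% | 5.4% / 6.1% / 5.4% |
| 80% vs 20% | 1.5 / 2 / 3 | 13.9% / 34.6% / 74.4% | 5.2% / 5.6% / 5.6% |

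The simulation standard error near 5% is √(0.05 × 0.95/1000) ≈ 0.7 percentage points, so the stratified column is compatible with 5% throughout. With no link between configuration and anatomy, the unadjusted test also behaves. The excess comes from the link.

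**2. Number of factors.** For k independent null factors, each tested at 0.05, the chance of at least one false positive is 1 − 0.95^k:

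- k = 5: 23%
- k = 10: 40%
- k = 20: 64%

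The article does not state k. Independence is assumed.

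**3. Technical success.** The cited series give 98.5% (603/612) and 99%. In 500 patients that is 500 × 9/612 ≈ 7.4 failures, or 500 × 0.01 = 5. With two groups of 250 and a twofold risk (0.98% vs 1.96%, or 0.67% vs 1.33%), power at 0.05 is about 15% or 11%.

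A log-rank test with every failure at time zero can still be computed. With 2 vs 6 failures per 250, it gives 2.028, and the Pearson chi-square is 2.033 (2.033 × 499/500 = 2.028; P = 0.154). Fisher's exact P is 0.285. The log-rank is thus a 2×2 chi-square in disguise, with too few events for its large-sample approximation.

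**4. How large a model the data could carry.** The cited report of 157 patients lists 5 type Ia endoleaks, 3 type Ib and 3 limb occlusions treated. Counted as separate patients, that is 11/157 = 7%, or about 35 in 500. An assumed 15% gives 75. At roughly 10 failures per parameter (a working convention), 35 to 75 failures support about 3 to 7 parameters.

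**The case against.** The strongest reply has four parts.

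- **The wording may already mean adjustment.** A reader might infer that factors will be tested one at a time, but the article does not say so. A stratified log-rank is a possible reading, and the table shows that it would control a measured binary confounder. This stands as a limit on the claim. Comparison between strata is still the more natural reading, and no stratifying variables are named. Stratifying on neck length, angle and diameter together would need cut-points and leave sparse strata.
- **Technical success is not mishandled.** A reader might infer that the log-rank is undefined for it, or that it has no valid analysis. The documents do not support this. Survival methods are introduced for time-dependent events, and cross tabulations with 95% confidence intervals cover a yes/no outcome. The test is also computable, as shown. What remains is that no suitable comparative test is named for it, and too few failures are expected to support one.
- **A model, factor list and multiplicity rule may sit in a document not shown.** Agreed. Their absence is not the point. The point is that the method the article does state does not fit the aim it states.
- **The sizes are built on assumptions.** Agreed. The 28% comes from an earlier series not described as restricted to the instructions for use, so it may be too high here. The configuration shares and hazard ratios have no source in the article. With a mild link (60% vs 40%), the excess is small unless anatomy matters a great deal.

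**Conclusion.** The concern holds in a limited form. For the question about configuration and baseline factors, the only stated comparison is stratification with a log-rank test at P<.05. If that means unadjusted comparisons between strata, it can report anatomy as a configuration effect, because components are chosen to fit anatomy.

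Under no true effect, the rejection rate ran from about 7% to 74% across the assumed scenarios, against 5% to 6% with stratification by the confounder. The direction follows from the article's own text, but the size is illustrative and is not an estimate for this cohort. The added false-positive risk from several factors is likewise a range (23% to 64% for 5 to 20 independent factors), because their number is not given. The point is worth correcting, since a stated secondary aim could otherwise be answered misleadingly.

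**What to change.** In Data Collection and Analysis:

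- For clinical failure, replace the log-rank test as the basis for conclusions with one prespecified multivariable cause-specific Cox model. Include configuration and a few anatomical and patient covariates, for example neck length, neck angle, aneurysm diameter, age and sex, in a stated order of priority. Keep the CT measurements continuous.
- Set in advance a rule that limits the parameters to the failures observed, for example about 3 to 7 for an assumed 35 to 75 failures.
- Report hazard ratios with 95% confidence intervals as exploratory, and drop the label of significance at P<.05. Keep Kaplan-Meier curves as description.
- Report technical success once, at the procedure, as a proportion with an exact confidence interval. Keep any association with it descriptive.

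The methods already call for diameter, length and angle on the preoperative CT angiogram, so the anatomical covariates need no new measurements. The cost is a change of wording, slightly more analysis and fewer factors called significant.

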### Patient Confidentiality

All information and data concerning patients or their participation in this clinical investigation will be considered confidential. Only authorized personnel will have access to these confidential files. Authorized personnel of health authorities will have the right to inspect and copy all records pertinent to this clinical investigation. All data used in the analysis and reporting of this clinical investigation will be anonymized.

## Results

The actual start date of the investigation was November 2019. It is anticipated that 500 patients will be recruited to the study. The final patient is expected to be treated by the end of December 2020 and the estimated study completion date is December 2025. After data analysis, results will be shared with each investigator.

## Discussion

In the last years, EVAR has become the standard of care for AAA treatment, and nowadays it represents the recommended modality of treatment according to the European Society for Vascular and Endovascular Surgery and the Society for Vascular Surgery guidelines [10,11].

However, the major randomized controlled trials (RCTs) on EVAR vs OR have not reached definitive conclusions. In 2004, the results of the first two RCTs were published [12,13].

The EVAR-1 trial described a clear advantage of EVAR compared to OR at 30 days. Greenhalgh and collaborators [12] reported that 30-day mortality in the EVAR group was 1.7% (9/531) vs 4.7% (24/516) in the OR group (*P*=.009). Their results were interpreted as a license to continue scientific evaluation of EVAR, but not to change clinical practice [12].

More enthusiastic conclusions came from the analysis of the Dutch Randomised Endovascular Aneurysm Management (DREAM) trial, reporting an operative mortality rate of 4.6% in the OR group (8/174 patients) and 1.2% in the EVAR group (2/171 patients) in a series of patients treated between 2000 and 2003, resulting in a risk ratio of 3.9 (95% CI 0.9-32.9). The combined rate of operative mortality and severe complications was 9.8% in the OR group (17/174 patients) and 4.7% in the EVAR group (8/171 patients), resulting in a risk ratio of 2.1 (95% CI 0.9-5.4). The authors concluded that EVAR was preferable to OR [13].

However, long-term follow-up was demanded to determine whether advantages persisted, and 1 year later, both trials published their midterm results [14,15]. In the EVAR-1 trial, all-cause mortality was similar in the two groups (approximately 28%; *P*=.46), but a persistent reduction in AAA-related deaths was recorded in the EVAR group compared with the OR group (4% vs 7%; *P*=.04). On the other hand, the proportion of patients with postoperative complications was 41% in the EVAR group and 9% in the OR group (*P*<.001) [14]. In the DREAM trial, 2 years after randomization, the cumulative survival rates were 89.6% for OR and 89.7% for EVAR and the cumulative rates of AAA-related deaths were 5.7% for OR and 2.1% for EVAR. This advantage of EVAR over OR was accounted for by events occurring in the perioperative period, with no significant difference in subsequent AAA-related mortality. The rate of survival free of moderate or severe complications was also similar in the two groups at 2 years (65.9% OR vs 65.6% EVAR) [15].

The Open Versus Endovascular Repair (OVER) trial, which included patients treated between 2002 and 2007, was published in 2010. On the basis of a mean follow-up of 1.8 years, the OVER trial results showed that perioperative mortality was lower for EVAR than for OR (0.5% vs 3.0%; *P*=.004), without any difference at 2 years (7.0% vs 9.8%, *P*=.13). Mortality after the perioperative period was similar in the two groups (6.1% vs 6.6%); however, 4 late deaths in the EVAR group were AAA-related compared with none in the OR group. No differences between the two groups in terms of major morbidity, procedure failure, secondary intervention, AAA-related hospitalization, or health-related quality of life were recorded. Interestingly, no increase in midterm mortality after EVAR resulted in the loss of early survival advantage as shown in previous trials was observed [16].

A year later, a French RCT (ACE Trial) reported quite different results with no differences between EVAR and OR. Although only low to intermediate risk patients were enrolled, OR and EVAR offered no difference in survival (96.5% vs 95.2% at 1 year, and 86.7% vs 86.3% at 3 years) or in major and minor complications (95.9% vs 93.2% at 1 year, and 85.1% vs 82.4% at 3 years) [17].

These results led to a change in point of view: EVAR was considered as feasible as OR without any advantages, even in the short-term. The same year, a new US study, with a 6-year follow-up on 45,652 Medicare beneficiaries undergoing EVAR or OR in the period between 2001 and 2004, was analyzed to clarify the late results of endovascular procedures. Throughout follow-up, overall reintervention or readmission rates were similar with the two repair methods but slightly more common after EVAR than OR (7.6 vs 7.0/100 person-years; *P*<.001). Overall 30-day mortality with any reintervention or readmission was 9.1%. EVAR patients had more AAA-related reinterventions than OR (3.7% vs 0.9%; *P*<.001; mortality 5.6%). Conversely, EVAR patients had fewer laparotomy-related reinterventions than OR patients (1.4% vs 3.0%; *P*<.001; mortality, 8.1%) and fewer readmissions without surgery (2.0% vs 2.7%; *P*<.001; mortality 10.9%). Overall, reinterventions and readmissions accounted for 9.6% of all EVAR deaths and 7.6% of all OR deaths in the follow-up period (*P*<.001). The authors concluded that reintervention and readmission were slightly higher after EVAR. Survival was negatively affected by reintervention or readmission after EVAR and OR [18].

In 2016, the long-term results of the EVAR-1 RCT were published. In a mean of 12.7 years for follow-up, Patel et al [19] reported a similar overall mortality in the EVAR and OR groups (9.3 deaths per 100 person-years vs 8.9 deaths per 100 person-years; hazard ratio (HR) 1.11, 95% CI 0.97-1.27). However, a time analysis showed that beyond 8 years after randomization OR had a significantly lower mortality (HR 1.25, 95% CI 1.00-1.56, for total mortality; and HR 5.82, 95% CI 1.64-20.65, *P*=.006 for aneurysm-related mortality) mainly due to secondary sac rupture. The authors concluded that the early benefits of EVAR in terms of mortality were lost in the long-term [19].

However, late results from the OVER trial were published. In Lederle’s [20] study, long-term overall survival was similar between patients who underwent endovascular repair and those who underwent OR (EVAR 68% vs OR 70%; HR 0.96, 95% CI 0.82-1.13). A difference between groups was noted in the number of patients who underwent secondary therapeutic procedures (EVAR 26.7% vs OR 19.8; 95% CI 2.0-17.5). Their results were not consistent with the findings of worse performance of endovascular repair with respect to long-term survival that was seen in the two European trials [20].

Notably, all these trials reported only few data or none at all on patients treated by unibody stent graft implantation. As mentioned above, AFX 2 Endovascular AAA System endografts are completely different from a technical and philosophical point of view from all other modular devices, and it seems to also provide different results. In fact, different studies have already demonstrated the advantages of this endograft and its safety and efficacy in short and midterm follow-up periods [1-5]. The preservation of the aortic bifurcation focuses the disrupting forces caused by columnar blood on the carrefour rather than on the aortic neck minimizing migration risk [1,2]. The obviation of contralateral gate cannulation makes this graft faster to deploy and uniquely suitable in cases of narrow aortic bifurcations. Moreover, this graft is allowed for future contralateral access for lower extremity interventions in a patient population with different vascular diseases. Finally, Dietrich et al [5] affirmed that the big contact area provided by the fabric free to move with the blood pressure wave can promote sac shrinkage and contrast type II endoleak formations.

Given the lack in current literature of effective data on unibody endograft results, the aim of our prospective study is addressing intraoperative, perioperative, and postoperative results in patients treated by the latest generation AFX 2 Endovascular AAA System endografts for elective AAA repair in a multicentric study.

